### Screening and randomization

The target population is patients with resectable FNCLCC G1/2 STS. After giving their written informed consent, patients fulfilling all inclusion and non-inclusion criteria (Table 1) will be enrolled in the study and molecular screening will be performed. After inclusion, an archived FFPE tumor sample of sufficient quantity will be sent to one of the four identified CINSARC signature platforms. Results of CINSARC analysis classifying patients as HR or LR-CINSARC will be provided by email to the investigator. After fulfilling additional inclusion criteria (HR-CINSARC signature, external radiotherapy not initiated before randomization (if applicable), full details in Table 1)), HR-CINSARC patients will be randomized by the sponsor to one of the two arms in a 1:1 ratio. Randomization will be stratified on the following factors: center, FNCLCC grade (grade 1 vs grade 2), tumor size (< 5 cm vs ≥5 cm), timing of chemotherapy envisaged (neo-adjuvant vs adjuvant) and histology (undifferentiated pleomorphic sarcoma vs dedifferentiated liposarcoma vs leiomyosarcoma vs synovial sarcoma vs other). A dynamic randomization procedure by minimization will be used. Randomization will be performed centrally by the IUCT-O clinical trials office using the TENALEA Clinical Trial Data Management System (online secure internet).

**Table 1 Tab1:** Inclusion and non-inclusion criteria

Inclusion Criteria	Non Inclusion criteria
- The regional platform will transmit the CINSARC status to the sponsor and will be provided to the investigator.According to FNCLCC grading system, grade 2 and grade 1 tumors - Resectable and localized disease after appropriate extension work-up (including at least a chest-CT) - Available archived FFPE tumor sample in sufficient quantity to allow CINSARC qualification - Age ≥ 18 years - Eastern Cooperative Oncology Group (ECOG) performance status ≤2 - Life expectancy of at least 12 weeks after the start of the treatment - Women should be post-menopaused or willing to accept the use an effective contraceptive regimen during the treatment period and at least 12 months after the end of the treatment period. All non-menopaused women should have a negative pregnancy test within 72 h prior to registration. Men should accept to use an effective contraception during treatment period and at least 3 months (Ifosfamide treatment) or 6 months (Dacarbazine treatment) after the end of the study treatment - Signed written informed consent - Patient affiliated to a Social Health Insurance in France **Additional criteria: Randomized Part** - High-risk CINSARC signature -External radiotherapy not initiated before randomization (if applicable). -Acceptable hematologic function (within 72 h prior randomization): Absolute neutrophil count (ANC) ≥ 1.5 G/L, Platelet count ≥100 G/L and Hemoglobin > 9 g/dL -Acceptable renal function within 72 h prior randomization: Serum creatinine ≤1.5 x ULN or calculated creatinine clearance ≥60 mL/min (by the Cockcroft and Gault formula) -Acceptable liver function: Bilirubin ≤1.5 x upper limit of normal (ULN), AST (SGOT) and ALT (SGPT) ≤ 2.5 x ULN -Normal LVEF (> 50%) measured by echocardiography or isotopic ventriculography	- Soft-tissue sarcoma with the following histological subtypes: well-differentiated liposarcomas, alveolar soft-part sarcoma, dermatofibrosarcoma protuberans, clear-cell sarcoma, epithelioid sarcoma, alveolar or embryonal rhabdomyosarcoma - Primitive cutaneous, retroperitoneal, uterus or visceral STS - Metastatic disease - Previous or ongoing treatment for the sarcoma (with the exception of a surgery for diagnosis intend) - Contra-indication for Doxorubicin, Ifosfamide and Dacarbazine treatments - Prior therapy with ifosfamide or cyclophosphamide or other nitrogen mustards, and prior therapy with anthracyclines - Prior mediastinal/cardiac radiotherapy - History or presence of clinically relevant cardiovascular abnormalities such as uncontrolled hypertension, congestive heart failure NYHA classification of 3, unstable angina or poorly controlled arrhythmia, myocardial infarction within 6 months prior to study entry - Prior or concurrent malignant disease diagnosed or treated in the last 2 years except for adequately treated in situ carcinoma of the cervix, basal or squamous skin cell carcinoma, or in situ transitional bladder cell carcinoma - Active, uncontrolled bacterial, viral, or fungal infections, requiring systemic therapy - Known infection with HIV, hepatitis B, or hepatitis C - Women who are breastfeeding, pregnant or who plan to become pregnant while in the trial - Concomitant disease or condition that could interfere with the conduct of the study, or that would, in the opinion of the investigator, pose an unacceptable risk to the subject in this study - Patient who has forfeited his/her freedom by administrative or legal award or who is under legal protection (curatorship and guardianship, protection of justice) - Patient unable to comply with the protocol for any reason.

LR-CINSARC patients will be included and treated at the discretion of the clinicians and data will be collected prospectively.

### CINSARC analysis

For each patient, a representative sample formalin-fixed paraffin-embedded (FFPE) tumor block from sarcoma tumor surgical resection or biopsy specimen (archived tissue) will be selected for molecular screening. Quality control of samples will be assessed by the investigational site pathologist and samples with less than 50% of tumor cells will be considered as non-eligible for CINSARC analysis (screen failure). Tumor samples passing quality control will be addressed to one of the four regional platforms.

CINSARC analysis will be performed using Nanostring technology [16, 17]. Briefly, unique multiplexed probes are made with two sequence-specific probes complementary to a 100-base target region per target mRNA. The capture probe comprises a target-specific oligonucleotide coupled with a short sequence linked to biotin. The reporter probe consists of a second 50mer target-specific oligonucleotide linked to a unique chain of dye-labeled segments for detection by the system. Our nCounter code set, named NanoCind®, includes a panel of 75 probes, including 67 distinct test probes derived from 67 distinct genes and eight housekeeping genes for normalization purposes. Probe sets were designed and synthesized by NanoString. Additional information concerning probes can be found in the patent, which is filed under the number EP18305190.3. This raw data can be uploaded to a web interface developed for this study and hosted by the Institute Claudius Regaud. The interface will calculate the CINSARC status: “LR” or “HR”. The regional platform will transmit the CINSARC status to the sponsor, who will send it in turn to the investigator.

### Treatment

#### Standard of care

HR-CINSARC patients randomized to the control arm and LR-CINSARC patients will be treated according to standard of care. Surgery will be performed according to standard guidelines by a surgeon in one of the investigational participating centers. If indicated, patients may be treated by external radiotherapy before or after excision surgery (if applicable) according to each participating center’s procedures and treatment guidelines.

#### Experimental treatment

Patients classified as HR-CINSARC randomized to the experimental treatment will be treated by standard of care with the addition of chemotherapy. They will receive 4 cycles of 3 weeks of intravenous chemotherapy with doxorubicin (20 mg/m2 per day [day 1, 2 and 3] every 3 week) in combination with dacarbazine (300 mg/m2 per day [day 1, 2 and 3] every 3 week)) for leiomyosarcoma or ifosfamide (3 g/m2 per day [day 1, 2 and 3] every 3 week) for other histologic subtypes.

### Follow-up

HR-CINSARC patients (Arm A or B) will be followed from the date of randomization, every 4 months the two first years and then every 6 months the next 3 years for a maximum of 5 years. According to treatment guidelines, assessments during this 5-year follow-up period will include at least clinical examinations of the tumor primary site and overall assessment/metastatic relapse assessment by CT scan. In the event of relapse, patients will be followed only for survival status until 5 years post-randomization.

Patients defined as LR-CINSARC will be followed up according to local practice and relevant prospective data (baseline characteristics, treatment, carcinologic event and survival status) will be collected for 5 years from the date of registration in the prospective cohort.

### Main statistical analysis

#### HR-CINSARC patients: randomized part

In G1/2 HR-CINSARC, the 3-year MFS was estimated around 60% [9, 10]. The main objective is to increase 3-year MFS from 60 to 75%, which corresponds to detecting a hazard ratio of 0.56. A total of 101 events is necessary for 80% power to detect this difference if it is true using a one–sided Logrank test at the 2.5% level of significance and a 1:1 randomization. Based on an estimated accrual rate of approximately 8 patients per month for the randomization of 250 patients with a fixed follow-up of 5 years, we expect to see this number of events 4.7 years after the start of the study.

Supposing 50% of G1/2 patients are HR-CINSARC [9], 500 patients with interpretable CINSARC results are required. With 15% of screen-failure (non-interpretable CINSARC result) or random-failure, 600 patients need to be included.

An interim analysis for both futility (O Brien Fleming boundary) and efficacy (O Brien Fleming boundary) will be performed after observation of 51 events [18]. The East software package (v6.4) will be used to calculate the appropriate bounds at the time of the analysis, given the fraction of information available. An independent data monitoring committee will review the pre-planned interim analyses (futility and efficacy). The planned discontinuation boundaries and decision rules are as follows:
50% of expected events (51 events):
◦ discontinuation for futility if one-sided *p*-value is > 0.282 (Hazard Ratio > 0.851)◦ discontinuation for efficacy if one-sided *p*-value is < 0.002 (Hazard Ratio < 0.438)◦ otherwise continue100% of expected events (101 events):
◦ claim success if one-sided *p*-value is < 0.024 (Hazard Ratio < 0.676)

The primary endpoint will be analyzed on the ITT population when the required number of events has been reached. The Kaplan-Meier approach will be used to estimate MFS rates for each treatment arm. Comparison between treatment arms will be performed using the Cox proportional hazards model with adjustment for stratification factors. Hazard ratios will be estimated with their 95% confidence interval (two-sided). The assumption of proportionality will be assessed graphically.

#### CINSARC prognostic value

In a retrospective study, the 3-year MFS was estimated to be 80 and 60% for LR and HR-CINSARC patients with FNLCC G1/2 [9, 10]. The main objective is to detect a hazard ratio of 2.1, which corresponds to a 3-year MFS equal to 80 and 63% in the LR and HR-CINSARC group, respectively. A total of 86 events is necessary for 90% power to detect this difference if it is true using a two–sided Logrank test at the 5% level of significance (it is assumed that 33% of G1/2 treated by standard of care are HR-CINSARC). Based on an estimated accrual rate of approximately 12 patients per month for the accrual of 375 patients treated by standard of care with a fixed follow-up of 5 years, we expect to see this number of events 4 years after the start of the study.

All patients FNCLCC G1/2 with interpretable CINSARC results will be treated according to standard of care. Survival rates (MFS, DFS and OS) will be estimated by CINSARC groups using the Kaplan-Meier method. Univariate analysis will be performed with the Logrank test. Variables associated with a univariate Logrank *p*-value less than 5% will be selected for multivariate analysis. Multivariate analysis will be performed with the Cox proportional hazards model to study the prognostic value of CINSARC groups on survival endpoints after adjusting for prognostic factors. Proportional hazards assumption will be assessed graphically.

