**Methods:**

CHIC is a parallel, randomized, open-label, multicenter study evaluating the effect on metastasis-free survival of adding perioperative chemotherapy to standard of care in patients with grade ½ STS sarcoma defined as HR by CINSARC. In this target selection design, 600 patients will be screened with CINSARC to randomize 250 HR-CINSARC patients between standard of care and standard of care plus chemotherapy (4 cycles of 3 weeks of intravenous chemotherapy with doxorubicin in combination with dacarbazine or ifosfamide according to histologic subtype). LR-CINSARC patients will be treated by standard of care according to the investigator. The primary endpoint is metastasis-free survival. Secondary endpoints include overall survival, disease-free survival and safety. Furthermore, the prognostic value of CINSARC will be evaluated by comparing LR-CINSARC patients to HR-CINSARC patients randomized in standard of care.

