### Trial design

This is a phase III, multicenter, randomized open-label comparative study that has been designed to demonstrate whether adding four cycles of perioperative doxorubicin-based chemotherapy (doxorubicin and ifosfamide or dacarbazine) improves MFS as compared with standard management in patients with resectable FNCLCC G1/2 STS, considered as HR according to CINSARC (ClinicalTrials.gov Identifier: NCT04307277).

After providing written informed consent, patients considered as eligible for the CHIC-STS study by the investigator will be enrolled and molecular screening will be performed to determine their classification according to CINSARC (LR or HR). To evaluate both the effect of chemotherapy in the subgroup of patients with an HR-CINSARC signature and the prognostic value of the CINSARC signature, this study is based on a target selection design [14]. Patients for whom tumor material has been qualified and CINSARC classification has been determined will be definitively enrolled according to their CINSARC classification results (Fig. 1).
Patients classified as HR by CINSARC signature (HR-CINSARC) will be randomized between standard of care (surgical excision +/− external radiotherapy) and the experimental arm (standard of care with chemotherapy)Patients classified as LR by CINSARC signature (LR-CINSARC) will be treated at the discretion of the clinicians and data will be collected prospectively.

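### The prognostic section wrongly says every classified patient receives standard of care, and the treatment of LR-CINSARC patients is described in two ways; state the analysis set and check for LR chemotherapy

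*Protocol article*

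**What the plan says.** Under 'CINSARC prognostic value', the protocol article states that "All patients FNCLCC G1/2 with interpretable CINSARC results will be treated according to standard of care". It then estimates survival by CINSARC group without saying that any randomised arm is left out.

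Other parts of the article describe the set differently:
- The abstract (Methods) says that "the prognostic value of CINSARC will be evaluated by comparing LR-CINSARC patients to HR-CINSARC patients randomized in standard of care".
- 'Secondary objectives' limits the prognostic question to patients given standard treatment.
- 'Trial design', 'Screening and randomization' and 'Experimental treatment' randomise HR-CINSARC patients 1:1, with chemotherapy added to standard of care in one arm.
- The sizing rests on "the accrual of 375 patients treated by standard of care with a fixed follow-up of 5 years", and "it is assumed that 33% of G1/2 treated by standard of care are HR-CINSARC".

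On LR-CINSARC treatment, 'Trial design' says these patients "will be treated at the discretion of the clinicians and data will be collected prospectively", and 'Screening and randomization' repeats this. 'Standard of care' says "HR-CINSARC patients randomized to the control arm and LR-CINSARC patients will be treated according to standard of care". The abstract joins the two ideas: standard of care, as the investigator sees it.

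**The concern.** Prospective validation of CINSARC is one of the two goals named in the Discussion. It is meant to show how the signature separates outcomes when treatment is the same in both groups. Three features of the text threaten that.

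1. The sentence that should define the analysis set is untrue. With 500 classified patients, 250 of them HR and randomised 1:1, about 125 are assigned chemotherapy. An analyst who took the sentence at its word would put all 250 HR patients in the comparison.
2. HR controls are assigned to an arm without chemotherapy. If clinicians' discretion allows chemotherapy in LR patients, and chemotherapy works, LR outcomes improve for a reason unrelated to the signature and the hazard ratio is overstated.
3. In Table 1, blood counts, renal and liver function and LVEF are required only for the randomised part. Metastasis-free survival (MFS) counts death from any cause, so a fitness check on HR patients alone could slightly lower their event rate.

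**Working it through.** **Which patients does the sizing assume?**

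Inputs from the prognostic section: hazard ratio 2.1, two-sided 5%, 90% power, 33% HR, 375 patients, 86 events, 12 patients per month. Inputs from the randomised-part section: 500 classified patients, 50% HR, 8 randomised per month. The 1:1 allocation is in 'Screening and randomization'.

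- Number: 250 LR + 250/2 HR controls = 375.
- Share: 125/375 = 33.3%.
- Accrual: 8 HR randomised per month gives 4 controls. With 50% HR there are also 8 LR per month. 4 + 8 = 12, as stated.
- Events (Schoenfeld): d = (1.960 + 1.282)² / [p(1-p)(ln 2.1)²], with (ln 2.1)² = 0.550.
  - p = 1/3: 10.51 / (0.2222 × 0.550) gives **86**, the plan's figure (87 if p = 0.33).
  - p = 1/2, all HR patients included: 10.51 / (0.25 × 0.550) gives **77**, which does not match.

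All four figures point to LR patients plus the HR control arm.

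**What would a literal analysis of all classified patients cost?**

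Assume the design effect of 0.56 for the treated half of HR patients, and 80% three-year MFS in LR.

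| HR control 3-year MFS | With chemotherapy | Mean of the two | Hazard ratio vs LR | Power at 86 events, p = 1/2 |
|---|---|---|---|---|
| 63% | 0.63^0.56 = 0.772 | 0.701 | ln 0.701 / ln 0.80 = 1.59 | Φ(√(86 × 0.25) × ln 1.59 - 1.96) ≈ 58% |
| 60% | 0.60^0.56 = 0.751 | 0.676 | ln 0.676 / ln 0.80 = 1.76 | ≈ 74% |

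Both control rates appear in the section: 60% as the retrospective estimate and 63% as the design value. The power figures hold events at 86, although 125 more patients would yield more events. They describe an analysis that the sizing and the abstract exclude.

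**What would chemotherapy in LR patients do?**

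The share f of LR patients treated is an assumption, since the document gives none. So is applying 0.56, which is the target effect in HR patients.

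Average-hazard approximation: LR hazard factor = 1 - f(1 - 0.56).
- f = 10%: 0.956, and 2.1/0.956 = 2.20.
- f = 20%: 0.912, and 2.1/0.912 = 2.30.

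Check on the survival scale. The stated rates give ln 0.63 / ln 0.80 = 2.07, slightly below the rounded 2.1. The LR rate becomes (1-f) × 0.80 + f × 0.80^0.56.
- f = 5%: hazard ratio 2.12.
- f = 10%: 2.17.
- f = 20%: 2.28.
- f = 30%: 2.40.

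The two calculations agree in direction and rough size.

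**The fitness criteria**

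The document gives no basis for a size. Only the direction can be reasoned: fewer deaths among HR controls would shrink the contrast, which is opposite to the effect of LR chemotherapy.

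**The case against.** The strongest reply is that this is a drafting slip. The abstract names the right comparison, the secondary objective is limited to standard treatment, and every sizing figure leaves the chemotherapy arm out. That stands. A reader might infer from the sentence that the plan pools chemotherapy-treated HR patients with controls and is underpowered for the prognostic goal; the document does not support this. A condensed article may also leave analysis-set detail to the full protocol. Even so, the published sentence is wrong, and nothing in that section corrects it.

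On LR patients, it can be said that discretion concerns surgery and radiotherapy. 'Research hypothesis' says chemotherapy is not currently part of grade 1/2 treatment, and the Discussion argues against it in LR disease. This makes widespread use unlikely. It does not settle the matter, because the Background describes chemotherapy as discussed case by case, and no text says whether discretion includes it. 'Follow-up' does provide for collecting LR treatment, so nobody need be treated as unexposed by default. However, the prognostic section does not say how those data will be used. Its Cox model adjusts for factors selected by univariate p-value and does not name treatment.

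It would also be too strong to infer that LR patients face no health filter. Performance status, life expectancy, contra-indications to the study drugs, cardiovascular history, infection and concomitant disease in Table 1 are applied before molecular screening and bind everyone. Only the laboratory and LVEF checks differ.

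**Conclusion.** The concern holds as an incorrect statement of the analysed population, together with an unreconciled description of LR treatment. The first changes no design figure: 375 patients, 86 events and 90% power stand once the set is read as LR plus HR controls. The dilution to about 1.6-1.8 is only the price of following the sentence literally.

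The second leaves a possible bias in favour of the signature. It is about 5-10% on the hazard ratio if 10-20% of LR patients receive chemotherapy and benefit as the design assumes for HR patients. Both conditions are assumptions, and the effect is nil if no LR patient is treated. The laboratory and LVEF asymmetry is minor, of unknown size, and tends to work against the signature. This is worth correcting because validating the signature is a main goal, but it is not a flaw in the design.

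**What to change.** 1. In 'CINSARC prognostic value', replace the sentence with: *The prognostic analysis includes all LR-CINSARC patients and the HR-CINSARC patients randomised to standard of care.*
2. Reconcile 'Trial design' and 'Screening and randomization' with 'Standard of care' on how LR patients are treated. Which description applies is for the sponsor to say.
3. Keep all LR patients in the main analysis. Add a sensitivity analysis that accounts for LR patients who received perioperative chemotherapy, using the treatment data already collected under 'Follow-up'. Such patients should not be dropped from the main set: those chosen for chemotherapy are likely to be at higher clinical risk, and removing them from one group only would create a new imbalance.

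The cost is a wording change and one extra sensitivity analysis. Sample size and events do not change, and no new data are needed.

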## Background

With an incidence of 4–5 cases / 1,000,000, soft tissue sarcomas (STS) are a group of rare heterogeneous tumors that develop from connective tissue cells. Their therapeutic management is based on multidisciplinary discussion at every step, starting with the need for a pre-therapeutic diagnostic biopsy. The key point in treating patients with localized STS is a large surgical resection to obtain a microscopically negative margin and remove all tumor cells. The quality of surgery remains the main risk factor for metastatic relapse. Neo-adjuvant or adjuvant treatments (radiotherapy and/or chemotherapy) are discussed case by case in a multidisciplinary meeting, depending on the presence of other prognostic factors such as histologic subtype, tumor size and FNCLCC (Fédération Nationale des Centres de Lutte Contre le Cancer) grade.

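### A univariate p<5% screen alone chooses the covariates for the CINSARC Cox model, so grade, size or histology can drop out by chance; the harm is modest and a fixed set is a cheap improvement

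*Protocol article*

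**What the plan says.** The section on CINSARC prognostic value (Main statistical analysis) plans three steps: Kaplan-Meier curves by CINSARC group for MFS, DFS and OS; univariate logrank tests; and a Cox model. Entry to the Cox model depends on the univariate result: variables with a p-value "less than 5% will be selected for multivariate analysis". The purpose of the model is "to study the prognostic value of CINSARC groups on survival endpoints after adjusting for prognostic factors". No variable is named as always included.

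The same section sizes the unadjusted comparison: "The main objective is to detect a hazard ratio of 2.1, which corresponds to a 3-year MFS equal to 80 and 63"% in the two groups. It continues: "A total of 86 events is necessary for 90% power to detect this difference", with a two-sided 5% logrank test, on the assumption that "33% of G1/2 treated by standard of care are HR-CINSARC", and "for the accrual of 375 patients treated by standard of care with a fixed follow-up of 5 years".

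Elsewhere the article treats the main clinical factors as known. The Background says that perioperative treatment is discussed "depending on the presence of other prognostic factors such as histologic subtype, tumor size and FNCLCC" grade. Screening and randomization stratifies on grade, size and histology, among other factors. The randomised comparison is adjusted for the stratification factors in advance.

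**The concern.** Patients are not randomised to a CINSARC class, so this is the comparison in the trial that is exposed to confounding. It is also the one in which a p-value from the same data decides what is adjusted for. A factor that is truly prognostic and associated with CINSARC can miss 5% by chance. Its effect then stays in the CINSARC hazard ratio.

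The more practical loss is one of interpretation. The article presents CINSARC as adding to histological grade, and its Discussion makes prospective validation of the signature one of two goals. If grade fails the screen, no planned analysis gives a CINSARC estimate adjusted for grade. The adjustment set could also differ between MFS, DFS and OS, which would make the three adjusted results hard to compare.

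This is not a detail left to an analysis plan that is not shown. The article states a positive rule, and a plan that follows it inherits the weakness.

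**Working it through.** **Inputs from the article:** hazard ratio 2.1, two-sided 5%, 90% power, 33% HR-CINSARC, 86 events, 375 patients. **Assumed, because the article gives none:** hazard ratios (1.3 to 2.5) and prevalences (10% to 50%) of the clinical factors, and their association with CINSARC.

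**1. The plan's own figure.** Schoenfeld events = (1.960 + 1.282)² / [p(1−p)(ln 2.1)²]. With p = 1/3: 10.51 / (0.2222 × 0.5505) = 85.9, so 86. With p = 0.33 the result is 87. The stated 86 reproduces.

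**2. Chance that a real factor fails the screen, if it is unrelated to CINSARC.** P(dropped) = 1 − Φ(√(86·q(1−q))·ln(hazard ratio) − 1.96), where q is the prevalence. For hazard ratio 1.5 and q = 0.5: √21.5 × 0.405 − 1.96 = −0.08, so 53%.

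| Hazard ratio | q = 50% | 30% | 20% | 10% |
|---|---|---|---|---|
| 1.3 | 77% | 80% | 84% | 89% |
| 1.5 | 53% | 59% | 68% | 80% |
| 2.0 | 10% | 16% | 27% | 51% |
| 2.5 | 1% | 3% | 8% | 28% |

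For an 80% chance of being kept, a factor needs a hazard ratio of exp[(1.960 + 0.842)/√(86·q(1−q))], which is 1.83 at q = 50% and 2.74 at q = 10%.

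If the analysis waited for 5 years on every patient, the stated MFS rates with exponential hazards give 250(1 − 0.80^(5/3)) + 125(1 − 0.63^(5/3)) ≈ 145 events. A factor with hazard ratio 1.5 would then still be dropped in 32% (q = 50%) to 69% (q = 10%).

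**3. The rule itself, by simulation** (375 patients, one third HR-CINSARC, analysis at 86 events; the Cox model after the screen against the model with all factors forced in).

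- *One confounder, hazard ratio 1.5, in 60% of HR-CINSARC and 35% of LR-CINSARC.* With no CINSARC effect it is dropped in about 53%. The rejection rate is 5.3% after the screen against 4.8% forced in, and the CINSARC hazard ratio is about 3-4% too high. With CINSARC hazard ratio 2.1 the factor is dropped in about 25%, because it picks up part of the CINSARC effect in its own univariate test. The mean CINSARC hazard ratio is then almost unchanged (2.14 against 2.13).
- *Three such confounders (hazard ratios 1.3-1.5), no CINSARC effect.* Bias is about 8-9% and the error 5.5-6.5%.
- *Four confounders (hazard ratios 1.3-2.0; prevalences in HR-CINSARC and LR-CINSARC of 90/60, 70/40, 40/20 and 60/35%).* With no CINSARC effect at least one is dropped in 88-89%, the mean CINSARC hazard ratio is 1.08-1.09 against 1.00, and the error rises from 4.3% to 5.9% or from 5.4% to 7.4%, depending on the hazard ratios. At CINSARC hazard ratio 2.1 at least one is dropped in 50-54%, but the estimate moves only from 2.13 to 2.15.
- *One factor with hazard ratio 1.5, less common in HR-CINSARC (35% against 60%), CINSARC hazard ratio 2.1.* It is dropped in about 83%, and the CINSARC hazard ratio is attenuated from 2.09 to 1.94.

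**4. Feasibility of a fixed model.** CINSARC 1 + grade 1 + size 1 + histology 4 (five groups) = 7 parameters; 86/7 ≈ 12 events each.

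**The case against.** The strongest objection is that the screen does little measurable harm. It omits a factor mainly when its observed effect is weak, and those are the data sets in which it confounds least. At the planned effect of 2.1, factors positively associated with CINSARC hardly move the estimate. The objective is secondary, and the test that was sized is an unadjusted logrank test that covariate selection does not touch. All of this stands, and it limits the point to an improvement.

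Three stronger readings are tempting, and the documents support none of them.

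- **About 11% inflation and 7% error for each omitted factor.** For the hazard ratio 1.5 confounder, (1 + 0.60 × 0.5)/(1 + 0.35 × 0.5) = 1.106. With a standard error of 1/√(86 × 2/9) = 0.229 the shift is 0.44 standard errors, which gives about 7.3% rejection. That describes a factor that is always left out. The planned rule with the same factor gives about 3-4% and 5.3%.
- **Grade or size will usually be dropped.** The rates of 53-59% for hazard ratio 1.5 hold for a factor unrelated to CINSARC, or roughly when CINSARC has no effect. With hazard ratio 2 or more and prevalence 30-50% the rate is 16% or less. The article gives no effect size for grade or size. It calls the grading system the best available predictor, yet also poorly informative for grade 2.
- **CINSARC could be screened out of its own model.** The literal wording allows it, but the stated purpose of the model makes CINSARC the exposure and the screened variables the adjusters.

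One might also expect clearly too narrow confidence intervals. With the single confounder and no CINSARC effect, simulated coverage was 94.7% against 95.0%.

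What the objection does not remove is that the rule can leave the trial without a grade-adjusted estimate, for no gain that the article states.

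**Conclusion.** The point holds as a modest weakness. The rule lets chance decide whether factors that the article already treats as prognostic enter the only planned adjusted analysis of CINSARC. Under the assumed values, one moderate confounder is lost in about a quarter of trials at the design effect and in about half if CINSARC has no effect. The numerical damage is small with one confounder and becomes noticeable only with several, or with a factor inversely related to CINSARC, where the estimate is pulled towards 1.

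These sizes depend on hazard ratios, prevalences and associations that the documents do not give, and on 86 MFS events. No event counts are given for DFS and OS, so nothing numerical is claimed for them. That no factor is forced in rests on the text alone and needs no assumption.

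**What to change.** For MFS, replace the screen by a Cox model fixed in advance: CINSARC, FNCLCC grade (1 or 2), tumour size (<5 or ≥5 cm) and histology in the five groups used for stratification. Keep all of them whatever their univariate p-values. Use the same set for DFS and OS if the event counts allow. Keep the univariate logrank results as description.

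The cost is wording, settled before outcome data are examined. Grade and histology are already needed for eligibility, size is a stratification factor, and baseline characteristics are collected in LR-CINSARC patients; whether size is among these should be confirmed. The downside is a few more parameters and slightly lower precision for the CINSARC hazard ratio. In the four-confounder simulation at hazard ratio 2.1, the adjusted test rejected in 86.0-86.5% with all factors forced in, against 87.9-89.1% after the screen. The event number and the sized logrank test do not change.
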